### Subgroup analyses

Pre-specified sub-group analyses will be performed using the dichotomous primary study endpoint described above. Sub-groups include ulcer site (categorical variable; fore-, mid- or hind foot, plantar/dorsal), WiFI Clinical Stage [27] at baseline presentation (categorical/ordinal variable; clinical stage 1–4), co-existent moderate to severe renal disease (dichotomous variable; creatinine clearance ≤30 mL/min, age (dichotomous variable; age ≤ 60 years) long term diabetic control at presentation (dichotomous variable; HbA1C ≤9%), primary surgical procedure performed (dichotomous variable; minor amputation vs. local sharp or surgical debridement).

### Interim analysis

Due to the long-time delay until the primary outcome can be ascertained for each patient, we plan a single interim analysis after the first 80 patients. We estimate that 78 (with continuity correction) patients are required to have 80% chance of detecting, as significant at the 1% level, an increase in the primary outcome measure from 45% in the control group to 85% in the spray-on skin group [19]. If this threshold is met, the trial will be ceased early. If this threshold is not met, the trial will be completed as described above.

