**Methods:**

One hundred and fifty eligible participants will be randomised to receive an autologous skin cell suspension, also termed ‘spray-on’ skin (ReCell®) or standard care interventions for their DFU. The primary outcome is complete wound healing at 6 months, but participants will be followed up for a total of 12 months to enable secondary outcomes including total overall costs, ulcer free days at 12 months and quality of life to be assessed.

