## Study design

This study is a prospective, randomised, open label trial powered for superiority. Local and international data informed sample size calculations indicating that, at present, 45% of patients with DFU will achieve complete healing at 6 months [17, 18, 21]. We estimate that 136 (with continuity correction) patients are required to have 80% chance of detecting, at the 5% level of significance, an increase in the primary outcome measure from 45% in the control group to 70% in the spray-on skin group [19]. To account for drop-outs, we will aim to recruit 150 participants in total.

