## Statistical considerations

### Primary and secondary outcomes

All analyses will be conducted according to the intention-to-treat principle. Baseline characteristics will be compared by treatment group. Effects of treatment on the primary study endpoint (complete healing of the index ulcer at 6 months) will be estimated with the use of unadjusted logistic regression with last observation carried forward for those lost to follow-up. All *P*-values will be two-sided and *P*-values less than 0.05 will be considered to indicate statistical significance. Multiple logistic regression will be applied to adjust for prognostic factors such as vascular insufficiency and site of DFU (fore-, mid- or hind foot) which are strongly correlated with the outcome (*r* ≥ 0.3) [25, 26]. Binary secondary outcomes at 12 months will be analysed similarly. For continuous secondary outcomes, change score analysis that determines treatment effect based on the difference between baseline and post treatment score (basic adjustment) will be undertaken. Multiple linear regression adjusting for i) the baseline value of the outcome variable in the model (model 1), and ii) model 1 + adjustment for prognostic baseline factors (model 2) will be undertaken. Data will be analysed using IBM SPSS Statistics 25.

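### The interim look uses 1% and the final test keeps the full 5%, so the design's nominal two-sided error is about 5.4%, slightly above the stated 5%

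*Protocol article*

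**What the plan says.** Under Study design, the sample size is set for 80% power to detect a rise in complete healing at 6 months from 45% to 70%, "at the 5% level of significance". The article adds: "We estimate that 136 (with continuity correction) patients are required". Recruitment is raised to 150 to allow for drop-out.

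Under Primary and secondary outcomes, the general testing rule is: "All *P*-values will be two-sided and *P*-values less than 0.05 will be considered to indicate statistical significance".

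Under Interim analysis, a single look is planned after the first 80 patients. It is justified by a calculation giving 78 patients for 80% power at the 1% level, for 45% against 85%. Two sentences then fix the decision rule: "If this threshold is met, the trial will be ceased early", and "If this threshold is not met, the trial will be completed as described above".

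**The concern.** Read together, these sections form a complete two-stage rule: success can be claimed at 1% after 80 patients, and if it is not, success can be claimed again at an undiminished 5%. A trial with no treatment effect gets two chances to succeed, so the overall false-positive rate must exceed that of the final test alone. This is a stated rule and not a detail deferred to an analysis plan, because the article itself sends the final analysis back to the unreduced 5% level.

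The primary efficacy claim is at stake. A final P value between about 0.046 and 0.05 would be called significant although the procedure behind it does not hold the advertised 5%.

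**Working it through.** **Inputs.** Final level 0.05, two-sided (Primary and secondary outcomes). Interim level 0.01 after 80 patients (Interim analysis), two-sided by the same general rule. Required total 136, planned total 150 (Study design). Equal allocation is assumed; it is not stated outright but fits two arms and even block sizes.

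**Reproducing the plan's figures.**

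- *Final N.* With mean rate 0.575, n per arm = [1.960·√(2·0.575·0.425) + 0.842·√(0.45·0.55 + 0.70·0.30)]² / 0.25² ≈ 60.2. The continuity correction (n/4)·[1 + √(1 + 4/(n·0.25))]² gives 68 per arm, or 136. A one-sided 5% test would give 110, so the 5% is two-sided.
- *Interim N.* With the pooled variance in both terms and mean rate 0.65, n = (2.576 + 0.842)²·2·0.65·0.35 / 0.40² ≈ 33.2. After continuity correction this is 39 per arm, or 78. The formula that yields 136 gives 74 here. That is a choice of formula and does not affect the point. The two-sided 1% reading is therefore consistent with the article's arithmetic.

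**Overall type I error.** Under no effect, the interim and final statistics Z1 and Z2 are approximately bivariate normal with correlation √t, where t is the information fraction. Overall error = 1 − P(|Z1| < 2.576 and |Z2| < 1.960).

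| Information fraction | Correlation | Overall error | Final level that restores 0.05 |
|---|---|---|---|
| 80/136 = 0.588 | 0.767 | 0.0535 | 0.0463 |
| 80/150 = 0.533 | 0.730 | 0.0542 | 0.0456 |

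The simple sum, 0.01 + 0.05 = 0.06, is only an upper bound, because the two looks share 80 patients.

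**Sensitivity to the reading of the rule.**

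- If the trial can stop only in favour of spray-on skin, the error is 0.0518 to 0.0521.
- If the threshold is an observed 40-point difference, then with 40 per arm z = 0.40/√(2·0.45·0.55/40) = 3.60, a nominal P of about 0.0003. The overall error is then about 0.0500.
- The two readings give quite different rules. Under true rates of 45% and 70%, the chance of stopping at the interim is about 37% at P<0.01 and about 10% with the 40-point rule.

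**Error of the planned test.** With the Wald test from logistic regression, binomial data and 40 per arm at the interim:

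| True healing rate in both arms | Final n per arm | Overall error |
|---|---|---|
| 45% | 68 | 0.051 |
| 45% | 75 | 0.053 |
| 50% | 75 | 0.049 |
| 60% | 68 | 0.049 |
| 60% | 75 | 0.056 |

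At 45% the final test alone has error 0.047 (68 per arm) and 0.049 (75 per arm), so the look adds about 0.003 to 0.004.

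**Price of the correction.** At 75 per arm and 45% against 70%, normal-approximation power is 88.0% at 0.05 and 87.2% at 0.0456. Repeating the sample-size calculation at the adjusted level gives 70 per arm, or 140.

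**The case against.** The best defence is that the excess is slight: at most 0.42 points in the normal approximation, and about half that if only benefit can stop the trial. In some configurations the planned Wald test stays under 5% even with the extra look, and a continuity-corrected test would stay well under it (0.031 to 0.041 for null rates of 35% to 65%). All of this is right. It rules out any claim that the error exceeds 5% in every circumstance, or that it rises by a full point. It does not rescue the rule: the conservatism comes from the discreteness of the data, and at a 60% healing rate with 75 per arm the error is 0.056.

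A second defence is that the threshold may be the 45%-to-85% difference, which leaves nothing to correct. The wording permits this, so the point is conditional on the 1% reading. That reading is the more natural, since the preceding sentence presents 85% as the effect to be detected and 1% as the level at which it is significant.

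A third is that 0.046 is not the only remedy. That is also right: a final P between 0.046 and 0.05 is not inherently wrong, because a much stricter interim boundary would leave almost all of the 5% for the end.

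A reader might also infer that stopping early would end follow-up and leave the cost-effectiveness hypothesis unanswerable. The article does not support this. It says that the trial would cease, not that randomised patients would no longer be followed, and the abstract commits to the contrary: "participants will be followed up for a total of 12 months to enable secondary outcomes including total overall costs". Study population and Follow up measurements likewise run to 12 months or 52 weeks. Counts of lost outcomes would need an assumed recruitment pace, and the Discussion reports that recruitment is slow. This is a wording matter to reconcile, not a shown error.

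**Conclusion.** The point stands in a limited form. As written, the two-look rule has a nominal two-sided type I error of about 0.0535 to 0.0542 against a stated 0.05. This rests on a two-sided 1% interim boundary at 80 patients, equal allocation, a final total of 136 to 150, and the normal approximation. The planned test's exact error ranged from about 0.049 to 0.056 over the cases checked. The discrepancy is small and would matter only for a borderline final result, but it concerns the primary claim and is cheap to remove. It should be fixed; it does not threaten the design.

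**What to change.** 1. Under Interim analysis, state that the boundary is two-sided P<0.01 on the adjudicated 26-week primary outcome of the first 80 randomised patients.
2. Under Study design, Primary and secondary outcomes, and Interim analysis, set the final primary test at about 0.046 (0.0456 at 80/150, 0.0463 at 80/136), recomputed from the actual information fraction, with a matching confidence interval of about 95.4%. Alternatively, keep the final test near 0.05 and adopt a much stricter interim boundary; a nominal level of about 0.0003 leaves the overall error at about 0.0500.
3. As a minor clarification, reconcile the sentence on ceasing the trial early with the 12-month follow-up in the abstract, Study population and Follow up measurements.

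The cost is wording plus, for the 0.046 option, about one point of power at 75 per arm. The continuity-corrected total for 80% power goes from 136 to about 140. The planned 150 covers this, but the drop-out margin falls from 150 − 136 = 14 to 150 − 140 = 10. The change should be made before any interim data are examined, so that it cannot appear to be driven by them.

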### Health economic analyses

The main perspective of the analyses will be societal. Direct health care costs including spray on skin and usual care treatment costs, hospital inpatient and outpatient costs, including hospital in the home, out-of-hospital medical services and consumables will be estimated. An incremental cost-effectiveness analysis will be performed in which the net costs and net effectiveness of spray on skin will be compared with those of usual care and expressed as ratios. All analyses and comparisons will be performed on an intention-to-treat basis. Since the time horizon for the primary endpoint (complete healing of the index ulcer) is 6 months, discounting will not be performed. The confidence intervals for the incremental cost-effectiveness ratio will be estimated using the bootstrap approach with 1000 repeated random samples drawn with replacement from the original data. Bootstrap confidence intervals will be constructed with the bias-corrected percentile method. Data will be analysed using IBM SPSS Statistics 25 [IBM Corporation].

Overall costs will be determined by length of hospital stay, number and nature of operating theatre visits, use of pathology and radiology services, length of “hospital in the home” treatment, direct antibiotic costs, consumables associated with wound management (dressings, debridement, human skin replacements, negative pressure wound therapy dressings; ambulatory nursing attendance, orthotic appliances (prostheses, casting, shoes, in-soles). To ascertain data on direct costs for outpatient home care nursing we will extract data from the ambulatory nursing services electronic data collection tool (COMCARE™ [Docobo]). Outpatient visit costs will be derived from Medicare rebates (for multidisciplinary team visits and single specialty attendances at podiatry, infectious diseases or vascular clinics), whilst drug costs will be estimated from listed drug costs from Pharmaceutical Benefits Scheme (PBS) published listing, or in the case of moxifloxacin, piperacillin-tazobactam, ertapenem and other non-PBS drugs, from direct pharmacy costs. All costs will be adjusted on a year-by-year basis according to the medical services component of the Consumer Price Index to a single financial year for comparisons (2018).

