**Discussion:**

Outpatient costs for dressings, home nursing visits and outpatient appointments are key cost drivers for DFU. If spray-on skin is effective, large cost savings to WA Health will be realised immediately through a shortened time to healing, and through a higher proportion of patients achieving complete healing. Shortened healing times may enable participants to return to work earlier. Any economic benefits are likely to be amplified across Australia and other similar demographic settings where aging populations with increased diabetes rates are considered major future challenges.

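### The economic analysis is labelled societal but costs only health-care items, states its uncertainty only as an interval on a ratio that may be negative, and does not fix one period for costs and effects

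*Protocol article*

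**What the plan says.** All references are to the protocol article.

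- **Perspective.** Health economic analyses states: "The main perspective of the analyses will be societal". The next sentence names what will be estimated: "Direct health care costs including spray on skin and usual care treatment costs, hospital inpatient and outpatient costs", followed by hospital in the home, out-of-hospital medical services and consumables. The next paragraph defines the total: "Overall costs will be determined by length of hospital stay, number and nature of operating theatre visits, use of pathology and radiology services", then hospital in the home, antibiotics, wound consumables, ambulatory nursing and orthotic appliances. Item ix of Secondary outcomes likewise describes inpatient and outpatient costs.
- **Uncertainty.** Net cost and net effectiveness are expressed as ratios, with 1000 bootstrap resamples. "Bootstrap confidence intervals will be constructed with the bias-corrected percentile method". No other measure of uncertainty is named.
- **Expected direction.** Rationale hypothesises faster healing and, through it, lower overall cost. The abstract's Discussion says that, if the treatment works, "large cost savings to WA Health will be realised immediately". Study design plans for 45% versus 70% healed.
- **Period.** "Since the time horizon for the primary endpoint (complete healing of the index ulcer) is 6 months, discounting will not be performed". The abstract's Methods extend follow-up to 12 months for "total overall costs, ulcer free days at 12 months and quality of life to be assessed".

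**The concern.** Cost-effectiveness is one of only two hypotheses in the article, so its perspective, its uncertainty measure and its time frame need to be fixed correctly.

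A societal perspective counts costs wherever they fall. A cost list confined to health services answers a narrower question, and a reader comparing the result with other societal analyses would be misled.

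A negative ICER arises when the treatment is better and cheaper, and also when it is worse and dearer. Within the negative range the size of the ratio does not track benefit. If the hypothesis of savings is right, the single planned uncertainty statement sits wholly or partly where it is hardest to read.

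If costs run to 12 months and healing is judged at 6, the ratio's numerator and denominator describe different periods unless the plan pairs them.

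**Working it through.** **1. Perspective: the passages side by side.** The label is societal. The defined costs are stay, theatre, pathology and radiology, hospital in the home, antibiotics, wound consumables, nursing and orthotics, with sources given for nursing, clinic visits and drugs. The list contains no productivity, informal-care or travel item, and Follow up measurements collects none. The abstract's Discussion names earlier return to work as a benefit, and the main Discussion describes travel as a barrier for patients. The label and the list do not agree.

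**2. Planning figures.** The economic section gives no cost figure to reproduce. The effect size used below comes from Study design. Its sample size reproduces: 45% versus 70%, two-sided 5%, 80% power, with continuity correction, gives 68 per arm, or 136 in total. I take 150 recruits as 75 per arm; the 1:1 ratio is implied, not stated.

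**3. Sign and order of the ratio.** ICER = ΔC/ΔE. The cost differences here are illustrations.

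| ΔC | ΔE (healed) | ICER |
|---|---|---|
| −$5,000 | +0.25 | −$20,000 |
| −$5,000 | +0.05 | −$100,000 |
| −$4,000 | +0.25 | −$16,000 |
| +$4,000 | −0.25 | −$16,000 |

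Rows 1 and 2: at the same saving, the smaller benefit has the more negative ratio. Rows 3 and 4: a dominant and a dominated result share one value.

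Incremental net monetary benefit, λΔE − ΔC, has neither problem. For any λ > 0, 0.25λ + 5,000 exceeds 0.05λ + 5,000, and 0.25λ + 4,000 is positive while −0.25λ − 4,000 is negative.

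**4. How close the effect difference comes to zero.** SE = √(0.45×0.55/75 + 0.70×0.30/75) = √(0.0033 + 0.0028) = 0.078. With an observed difference of 0.25, z = 0.25/0.078 ≈ 3.2, so about 0.07% of replicates have a non-positive effect.

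**5. Behaviour of the planned interval.** The simulation used 400 trials per setting, 75 per arm, 1000 resamples and a 95% bias-corrected percentile interval. Assumptions, because the article gives no costs: gamma-distributed costs, control mean 20,000, coefficient of variation (CV) 0.75 to 1.5, saving 0 to 4,000, and cost independent of healing within arm.

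| True healing | Saving | CV | Share of replicates cheaper and better | Share dearer and better | Coverage |
|---|---|---|---|---|---|
| 45% v 70% | 4,000 | 0.75–1.5 | 74–89% | 10–25% | 95–96% |
| 45% v 70% | 0–4,000 | 0.75–1.5 | 49–89% | 10–50% | 93–98% |
| 45% v 60% | 4,000 | 1 | 78% | 15% | 92% |
| 45% v 55% | 4,000 | 1 | 69% | 14% | 79% |

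At 45% versus 70%, more than one quadrant of the cost-effect plane held over 2.5% of replicates in 57% to 84% of trials with a saving of 4,000, and in 84% to 93% with a saving of 2,000. At 45% versus 55%, about 17% of replicates (2.5% + 14.7%) had a negative effect difference, and some reached zero, so a limit could become arbitrarily large.

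**6. Discounting.** Costs spread evenly over a year shrink by 1 − [1 − 1/(1+d)]/ln(1+d): 1.5% at d = 3% and 2.4% at d = 5% (assumed rates). Omitting discounting matters little at 12 months.

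**The case against.** **The interval is usable in the planned scenario.** When almost all replicates have a positive effect difference, the ratio is ordered across zero cost. A ratio below the threshold then means positive net benefit, and a negative upper limit indicates dominance. This stands. A reader might infer that the interval is meaningless in exactly the case the trial hopes for. The near-nominal coverage at 45% versus 70% does not support that. What remains is that the size of a negative ratio misleads and that the interval degrades when the effect is smaller.

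**A negative ICER is not certain.** The abstract's statement about savings is conditional, the second hypothesis claims cost-effectiveness and not saving, and the main Discussion speaks of additional costs sensitive to the product's price. This also stands. It means that the sign of the cost difference is open, which is itself a reason not to rely on a ratio interval alone.

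**The 6 months is not a cost horizon.** A reader might infer that the economic analysis stops at 6 months and so ignores re-ulceration and later healing in the control arm. The sentence gives 6 months as the primary endpoint's horizon, as a reason not to discount. No passage cuts costs off there.

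**The article is condensed.** Net benefit and acceptability curves may appear in a fuller plan, and their absence alone would be no finding. The perspective label and the interval method, however, are stated choices. The wording of the first cost sentence leaves some room for further items, but the definition of overall costs reads as closed. The article does not say who pays for orthotic appliances, so it cannot be claimed that no patient payment is counted.

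**Conclusion.** The point holds in three parts of unequal weight.

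- **Perspective: a plain contradiction.** As written, a health-care-sector result would be reported as societal. This rests on the text alone.
- **Uncertainty measure: a poor choice with a cheap, better alternative.** The sign and order problem is arithmetic and needs no assumption. The loss of coverage, to about 79% at 45% versus 55% but not at the planned effect, rests on assumed costs.
- **Period: a loose end.** Costs followed to 12 months and healing judged at 6 months are not explicitly paired. The lack of discounting is harmless.

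The change should be made before the economic analysis. The primary efficacy analysis and the sample size do not depend on it.

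**What to change.** 1. Name the main perspective health-care sector. Alternatively, keep societal and add productivity, informal-care and travel costs. Relabelling is a wording change and narrows the claim. Keeping the label requires collecting data that the article does not describe.
2. From the same 1000 bootstrap samples, report incremental cost and incremental effect with their joint distribution, incremental net monetary benefit with a confidence interval over stated threshold values, and a cost-effectiveness acceptability curve. Give the ICER as a point estimate only, and state dominant or dominated where that applies. This is minor programming and needs no new data.
3. State one period over which costs and effects are paired, for example 12 months, when total costs and ulcer-free days are already followed. Base the case for not discounting on that period. This costs one sentence.

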### Data management procedures

Study data will be collected and managed using REDCap [9.2.5 Vanderbilt University] electronic data capture tools hosted at the University of Western Australia [28].

